### 10.3.2. Efficacy Analyses

The objective response rate (ORR), disease control rate (DCR), duration of response (DoR), PFS per investigator assessment and the corresponding CI, will be provided by cohort (according to RECIST v1.1 for disease progression). Time-to-event variables, such as DoR, PFS, and OS, will be estimated by Kaplan-Meier (1958) methodology by cohort. Presentations of preliminary efficacy may include patients enrolled in DLT Phase 1a with the same tumor type and dosing scheme. Individual changes in the tumor burden over time will be presented graphically within a tumor type (that is, Waterfall plots). Subgroup analysis of interest will be further defined in the Statistical Analysis Plan (SAP). The details of PFS censoring scheme by RECIST 1.1 are presented below.

**Table JPCE.10.2. PFS Event/Censoring Scheme by RECIST 1.1**

| Situation a                                                                                                                                                                        | Event/Censor | Date of Event or Censor                                                                                                                              |
|-----------------------------------------------------------------------------------------------------------------------------------------------------------------------------------------------|--------------|------------------------------------------------------------------------------------------------------------------------------------------------------|
| Tumor progression or death                                                                                                                                                                    | Event        | Earliest date of PD or death                                                                                                                         |
| No tumor progression and no death                                                                                                                                                             | Censored     | Date of last adequate radiological assessment or date of first treatment (whichever is later) b                                           |
| Unless                                                                                                                                                                                 |              |                                                                                                                                                      |
| No baseline radiological tumor assessment available                                                                                                                                           | Censored     | Date of first treatment                                                                                                                              |
| No adequate postbaseline radiological tumor assessment available and death reported after 2 scan intervals following first treatment b,c                                           | Censored     | Date of first treatment                                                                                                                              |
| New anticancer treatment started and no tumor progression or death within 14 days                                                                                                             | Censored     | Date of last adequate radiological assessment prior to (start of new therapy + 14 days) or date of first treatment (whichever is later) b |
| Patient lost to follow-up (or withdrew consent from study participation) before documented progression or death                                                                               | Censored     | Date of last adequate radiological assessment or date of first treatment (whichever is later) b                                           |
| Tumor progression or death documented immediately after 2 or more scan intervals following last adequate radiological tumor assessment or first treatment (whichever is later) b,c | Censored     | Date of last adequate radiological assessment or date of first treatment (whichever is later) b                                           |

Note: Progression-free survival and associated outcome are determined by the earliest of the dates above, if more than 1 situation applies.

Abbreviations: CR = complete response; PD = progressive disease; PFS = progression-free survival; PR = partial response; RECIST 1.1 = Response Evaluation Criteria in Solid Tumors Version 1.1; SD = stable disease.

a Symptomatic deterioration (that is, symptomatic progression that is not radiologically confirmed) will not be considered as tumor progression.

b Adequate radiological tumor assessment refers to an assessment with one of the following responses: CR, PR, SD, or PD.

c Refer to the statistical analysis plan for the definition of 2 scan intervals, including any adjustment for scan window.

### **10.3.3. Primary Outcome and Methodology (Safety and Tolerability)**

The primary objective is to evaluate safety and tolerability of abemaciclib in combination with pembrolizumab. All patients who receive at least 1 dose of study treatment will be evaluated for safety and toxicity. Adverse event terms and severity grades will be assigned by the investigator using CTCAE, Version 4.0.

Safety analyses will include summaries of the following:

- The CTCAE Version 4.0 term reported by the investigator will be mapped to the Medical Dictionary for Regulatory Activities (MedDRA) Preferred Term (PT) and System Organ

Class (SOC) using the corresponding MedDRA Lower Level Term (LLT), unless the reported CTCAE term is ‘Other – specify.’

- If the reported CTCAE term is ‘Other – specify,’ the MedDRA LLT, PT, and SOC centrally mapped from the verbatim AE term will be used.
- All listings and summaries will use the PT resulting from this process.

Preexisting conditions are defined as AEs that begin prior to the first dose of study drug.

A treatment-emergent adverse event (TEAE) is defined as an event that first occurred or worsened in severity after baseline. Comparisons of preexisting conditions to on-treatment events at the LLT level will be used in the treatment-emergent computation. The following summaries will be produced by PT within SOC: preexisting conditions, SAEs, TEAEs, drug-related TEAEs, and procedure-related TEAEs.

The following summaries will be produced by PT within SOC and maximum CTCAE grade: laboratory-based TEAEs, nonlaboratory-based TEAEs, drug-related laboratory-based TEAEs, and drug-related nonlaboratory-based TEAEs.

Reasons for death will be summarized separately for on-therapy and within 30 days of treatment discontinuation.

Hospitalizations and transfusions during the study treatment period or during the 30-day short-term follow-up period will be summarized by cohort.

#### **10.3.4. Other Analyses**

##### **10.3.4.1. Disposition**

A detailed description of patient disposition will be provided. It will include a summary of the number patients treated, as well as number and percentage of patients completing the study or discontinued (overall and by reason for discontinuation) treated patients. All patients received treatment will be accounted for in the summation. In addition, the number of patients who are screen failures and the reason for screen failure will be summarized.

A summary of all important protocol deviations will be provided.

##### **10.3.4.2. Patient Characteristics**

Patient characteristics at baseline will be summarized by cohort:

- Patient demographics
- Baseline disease characteristics
- Historical illnesses
- Prior anticancer therapy

Other patient characteristics will be summarized as deemed appropriate

##### **10.3.4.3. Concomitant Therapy**

Concomitant medications will be summarized for the safety population.

**10.3.4.4. Treatment Compliance**

The number of dose omissions, reductions, and delays, cycles received, and dose intensity will be summarized for all treated patients per treatment arm. Treatment compliance information for study drug will be collected through solid oral dosage unit counts at each tumor assessment visit. The estimate of percent compliance will be given by:

$$\text{Percent Compliance} = \frac{\text{Dose Taken}}{\text{Dose Dispensed}} \times 100$$

The actual cumulative dose taken will be determined based on counting the number of solid oral dosage units returned at each visit and subtracting that number from the number of dosage units dispensed. The expected cumulative dose to be taken will be determined based on the assigned dose and taking into account any dose reductions or omissions.

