| Study Drug                                  |                                |   |                                          |   |                                                                                                                                                                                                                                                                                             |
| Abemaciclib                                        | Daily every 12 hours           |   |                                          |   | Abemaciclib is to be administered every 12 hours on Days 1 through 21 of each cycle.                                                                                                                                                                                                        |

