## 7.6. Treatment Compliance

Patient compliance with abemaciclib will be assessed by counting returned solid oral dosage units. Study medication administration data will be recorded in the patient's medical record and eCRF.

Patients who are significantly noncompliant will be discontinued from the study. A patient will be considered significantly noncompliant if he or she misses 7 or more consecutive days of abemaciclib (full doses), or more than 25% cumulative days of abemaciclib (full doses) during the study. Similarly, a patient will be considered significantly noncompliant if he or she is judged by the investigator to have intentionally or repeatedly taken more than the prescribed amount of medication. Abemaciclib dose suspensions or delays related to toxicity may occur and will not result in a patient being considered as noncompliant.

Pembrolizumab will be administered only at the investigational sites by authorized study site personnel. As a result, treatment compliance is ensured.

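### The abemaciclib compliance percentage divides by dose dispensed and leaves the defined expected dose unused, so returned tablets from protocol-directed holds score like missed doses (minor, descriptive only)

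*Protocol*

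**What the plan says.** Protocol Section 10.3.4.4 plans to summarize omissions, reductions, delays, cycles received and dose intensity, and then adds a percent compliance. Its numerator is dose taken and its denominator is "Dose Dispensed". Tablet counts are collected "through solid oral dosage unit counts at each tumor assessment visit". Dose taken is found by counting returned units and "subtracting that number from the number of dosage units dispensed".

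The section closes by defining one more quantity: "The expected cumulative dose to be taken will be determined based on the assigned dose and taking into account any dose reductions or omissions". It appears in neither the numerator nor the denominator of the printed formula.

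Section 7.6 deals with compliance for patient management. It treats as significantly noncompliant a patient who "misses 7 or more consecutive days of abemaciclib (full doses), or more than 25% cumulative days of abemaciclib (full doses) during the study", and it adds: "Abemaciclib dose suspensions or delays related to toxicity may occur and will not result in a patient being considered as noncompliant".

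**The concern.** A compliance percentage should separate doses the patient failed to take from doses the patient was told not to take. The expected dose defined in Section 10.3.4.4 would do that, because it allows for reductions and omissions. The printed denominator does not: a returned tablet lowers the percentage whether it was held on instruction, left over after a reduction, spare, or simply missed.

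Table JPCE.7.2 makes suspension mandatory for many toxicities, and Table JPCE.7.4 allows up to 14 days for recovery. Patients with the most toxicity-related holds would therefore tend to get the lowest percentages. A reader of the compliance table could take managed toxicity for poor adherence.

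**Working it through.** The protocol states no compliance figure, so there is none to reproduce. The check is to evaluate the printed formula for a patient who takes every instructed dose.

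**Inputs from the protocol**
- Two doses a day: "Abemaciclib is to be administered every 12 hours on Days 1 through 21 of each cycle" (Table JPCE.2.2).
- Count interval of 6 weeks = 42 days, hence 42 × 2 = 84 doses (tumor assessment schedule for the first 48 weeks, Table JPCE.2.2).
- Toxicity recovery of up to 14 days (Table JPCE.7.4).
- 24 weeks = 168 days, the treatment period behind the analysis in Section 10.3.1.

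**Assumptions**
- Doses for the held days had already been dispensed.
- There is no spare supply unless stated. The protocol gives no dispensing quantity, so 3 and 7 days' spare are shown as a range.
- Dose reductions are not quantified, because the protocol gives no abemaciclib tablet strengths.

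**Formulas**
- Printed: taken = dispensed − returned, so the percentage is 100 × (dispensed − returned) / dispensed = 100 × (1 − returned/dispensed). The expected dose does not enter.
- Alternative: 100 × taken / expected, with expected = assigned doses less protocol-directed omissions.

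**One 42-day interval, in doses**

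| Situation | Taken | Dispensed | Printed | Expected | Taken/expected |
|---|---|---|---|---|---|
| 14-day directed hold | 56 | 84 | 66.7% | 56 | 100% |
| 7-day directed hold | 70 | 84 | 83.3% | 70 | 100% |
| 7 days missed by the patient, no hold | 70 | 84 | 83.3% | 84 | 83.3% |
| No hold, 3 days' spare | 84 | 90 | 93.3% | 84 | 100% |
| No hold, 7 days' spare | 84 | 98 | 85.7% | 84 | 100% |

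The second and third rows show the defect: the printed formula gives 83.3% to both a directed 7-day hold and 7 days of missed doses. The expected-dose denominator separates them.

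**Cumulatively over 24 weeks, in days**
- One 14-day hold: (168 − 14)/168 = 154/168 = 91.7%.
- One 7-day hold: (168 − 7)/168 = 161/168 = 95.8%.

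Both should be 100% for this patient.

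**A trap in the existing definition.** The expected dose allows for any omission, whatever its cause. If doses missed by the patient were also netted out, the patient in the third row would score 70/70 = 100% and real noncompliance would disappear. The denominator has to net out directed omissions only.

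**The case against.** The strongest reply is that this is a mislabelled denominator. The section defines actual and expected dose directly under the formula, and a statistician might compute the ratio of the two in any case. That is a likely reading of the intent, but the printed formula says otherwise and the two need reconciling. Three further points against the concern stand:

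- The 66.7% is a single-interval figure. Section 10.3.4.4 speaks of cumulative dose, and one hold is diluted over a longer period, as the 24-week figures show.
- If a hold takes the form of a delayed cycle start, the tablets for that time may not have been dispensed, and the ratio then loses nothing.
- Omissions, reductions, delays and dose intensity are summarized in their own right, so holds remain visible to the reader.

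Stronger readings are tempting, but the documents do not support them:

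- A reader might infer that the formula contradicts the Section 7.6 discontinuation rule or could cause a patient to be withdrawn. That rule counts missed days, exempts toxicity holds and does not use this percentage. The conflict is one of principle. The exemption also names only suspensions and delays; reductions are covered only by the expected-dose sentence.
- A reader might infer that the tolerability conclusion or the exposure-response objective is distorted. The safety analysis in Section 10.3.3 does not use compliance, and Section 10.3.4.5 links response to exposure through a population pharmacokinetic model.
- A reader might infer two conflicting counting schedules, because the section first names tumor assessment visits and later just visits. The later mention reads naturally as the visits already named. Counting at every Day 1 visit would be a preference.

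**Conclusion.** The point holds as a wrong printed formula. Section 10.3.4.4 defines the quantity that belongs in the denominator and then does not use it, so directed holds of tablets already dispensed cannot be told apart from missed doses.

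For a fully adherent patient with one 14-day hold, the understatement is 33.3 percentage points over one 42-day interval (100 − 66.7) and 8.3 points over 24 weeks (100 − 91.7). Both figures assume that full supply was dispensed. The spare-supply effect, 6.7 to 14.3 points over 42 days for 3 to 7 days' spare, is an illustration only.

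The consequence is limited to a descriptive summary in a single-treatment, non-comparative study. No endpoint, decision rule or discontinuation rule depends on it. Severity is minor.

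**What to change.** In Section 10.3.4.4, replace the dispensed dose in the denominator with the expected cumulative dose already defined there. Qualify that definition so that only protocol-directed reductions, suspensions and delays are netted out and doses missed by the patient stay in. The planned dose-intensity summary can remain as it is.

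The cost is one formula and one qualifying phrase, with no new visit or procedure. Section 7.6 already has administration data recorded in the eCRF, and Section 9.2 already requires dose modifications resulting from adverse events to be reported there. Under Section 10.3.1, an analysis change that does not alter a principal feature of the protocol needs no amendment. It can be described and justified in the clinical study report.

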**10.3.4.5. Pharmacokinetics**

Abemaciclib PK analyses will be conducted on all patients who have received at least 1 dose of study treatment and have had samples collected (see PK sampling schedule in [Appendix 4](#)).

Mean population PK parameters for abemaciclib in plasma and inter-individual PK variability will be computed using nonlinear mixed-effect modeling implemented in NONMEM. Likewise, if warranted by the data, mean population PK parameters for pembrolizumab in serum will be computed using nonlinear mixed-effect modelling.

Pharmacodynamic data (such as response rate, change in tumor size, PFS, OS, neutrophils, or diarrhea) collected in this study may be analyzed by means of NONMEM and connected to the population PK model for abemaciclib and/or pembrolizumab in a PK/pharmacodynamic model.

**10.3.4.6. Biomarkers**

Biomarker analyses will be based on the subset of patients from the above cohorts from whom a valid assay result (according to laboratory guideline) has been obtained. Correlative analyses will be performed to investigate associations between biomarkers and clinical endpoints as deemed appropriate.

An exploratory objective of this study is to evaluate biomarkers related to mechanism of action of abemaciclib and/or pembrolizumab, pathogenesis of cancer, immune modulation, and associations with clinical and/or safety outcomes. A corresponding exploratory objective for paired biopsies is to assess the change in expression from baseline for the biomarkers of interest to evaluate target engagement. From a statistical perspective, assuming that the standard deviation of the paired expression changes is roughly twice as large as its average, a sample size of 25 paired samples would provide ~ 70% power to detect a clinically meaningful reduction or increase in expression (say 30%) at a significance level of 5%. However, the power would be ~55% or lower if the number of paired samples available is 20 or fewer.

**10.3.4.7. Health Outcomes**

Change from baseline in MDASI scores will be listed and summarized for each study part at each postbaseline time point specified in the study schedule. Resource utilization will be described as appropriate.

**10.3.4.7.1. Health Outcomes and Economics**

For the MDASI\* questionnaire (that is, the 19 core MDASI items with 2 supplemental items: one for cough and one for diarrhea) that is used in this study to collect patient self-reported information on disease and treatment-associated symptoms, along with consequent or coincident interference with affective dimensions (that is, mood, relations with others, and enjoyment with life) and activity dimensions (that is, walking, general activity, and work), the compliance rate by treatment arm will be calculated as the number of completed assessments divided by the number of expected assessments (that is, patients still on study). Compliance rates, reasons for noncompliance, and data collected for each instrument will be summarized by treatment arm.

The MDASI core (MDASI; Cleeland et al. 2000) plus 2 added items (that is, the MDASI\*) single-item scores and changes from baseline will be listed. Changes from baseline will be summarized at each postbaseline time point specified in the study schedule. The summary at each post baseline time point will include mean, median, and standard deviation.

Resource use data will be summarized with descriptive statistics. If modeling is indicated, the appropriate methods will be used for the level of data measurement captured (for example: count data to be modeled with Poisson or negative binomial regression).

**10.3.5. Subgroup Analyses**

Subgroup analyses of interest will be further defined in the SAP.

**10.3.6. Interim Analyses**

An interim analysis of safety and preliminary efficacy may occur for each cohort after all patients in the given cohort have completed (or discontinued from) approximately 24 weeks of treatment. Any cohort-specific interim analyses may be combined if they are expected to occur within approximately a month, and interim analyses may also be combined with the ongoing trial-level safety review or annual safety review for annual safety update reporting.

## Appendix 1. Abbreviations and Definitions

| Term                                     | Definition                                                                                                                                                                                                                                                                                                                                                                                                                                                                                              |
|------------------------------------------|---------------------------------------------------------------------------------------------------------------------------------------------------------------------------------------------------------------------------------------------------------------------------------------------------------------------------------------------------------------------------------------------------------------------------------------------------------------------------------------------------------|
| ADA                               | anti-drug antibody                                                                                                                                                                                                                                                                                                                                                                                                                                                                                      |
| AE                                | Adverse event: any untoward medical occurrence in a patient or clinical investigation patient administered a pharmaceutical product and that does not necessarily have a causal relationship with this treatment. An adverse event can therefore be any unfavorable and unintended sign (including an abnormal laboratory finding), symptom, or disease temporally associated with the use of a medicinal (investigational) product, whether or not related to the medicinal (investigational) product. |
| ALT                               | alanine aminotransferase                                                                                                                                                                                                                                                                                                                                                                                                                                                                                |
| AST                               | aspartate aminotransferase                                                                                                                                                                                                                                                                                                                                                                                                                                                                              |
| CIOMS                             | Council for International Organizations of Medical Sciences                                                                                                                                                                                                                                                                                                                                                                                                                                             |
| collection database               | a computer database where clinical trial data are entered and validated.                                                                                                                                                                                                                                                                                                                                                                                                                                |
| CRP                               | Clinical research physician: Individual responsible for the medical conduct of the study. Responsibilities of the CRP may be performed by a physician, clinical research scientist, global safety physician, or other medical officer.                                                                                                                                                                                                                                                                  |
| CTCAE                             | Common Terminology Criteria for Adverse Events                                                                                                                                                                                                                                                                                                                                                                                                                                                          |
| CYP                               | cytochrome P450                                                                                                                                                                                                                                                                                                                                                                                                                                                                                         |
| DCR                               | disease control rate                                                                                                                                                                                                                                                                                                                                                                                                                                                                                    |
| DoR                               | duration of response                                                                                                                                                                                                                                                                                                                                                                                                                                                                                    |
| ECG                               | Electrocardiogram                                                                                                                                                                                                                                                                                                                                                                                                                                                                                       |
| ECI                               | Events of Clinical Interest                                                                                                                                                                                                                                                                                                                                                                                                                                                                             |
| ECOG                              | Eastern Cooperative Oncology Group                                                                                                                                                                                                                                                                                                                                                                                                                                                                      |
| eCRF                              | electronic case report form                                                                                                                                                                                                                                                                                                                                                                                                                                                                             |
| effective method of contraception | 
Effective method of contraception means male condom with spermicide, female condom with spermicide, diaphragm with spermicide, cervical sponge, or cervical cap with spermicide.
 
Also see the definition of highly effective method of contraception.
                                                                                                                                                                                                                                     |
| enroll                            | The act of assigning a patient to a treatment. Patients who are enrolled in the trial are those who have been assigned to a treatment.                                                                                                                                                                                                                                                                                                                                                                  |

| Term                                            | Definition                                                                                                                                                                                                                                                                                                                                                                                         |
|-------------------------------------------------|----------------------------------------------------------------------------------------------------------------------------------------------------------------------------------------------------------------------------------------------------------------------------------------------------------------------------------------------------------------------------------------------------|
| enter                                    | Patients entered into a trial are those who sign the informed consent form directly or through their legally acceptable representatives.                                                                                                                                                                                                                                                           |
| ERB                                      | ethical review board                                                                                                                                                                                                                                                                                                                                                                               |
| GCP                                      | good clinical practice                                                                                                                                                                                                                                                                                                                                                                             |
| HER2                                     | human epidermal growth factor receptor 2                                                                                                                                                                                                                                                                                                                                                           |
| highly effective method of contraception | combined oral contraceptive pill and mini-pill, NuvaRing®, implantable contraceptives, injectable contraceptives (such as Depo-Provera®), intrauterine device (such as Mirena® and ParaGard®), contraceptive patch for women <90 Kg (<198 pounds), total abstinence, or vasectomy.

Also see the definition of effective method of contraception.                                            |
| H&P                                  | history and physical                                                                                                                                                                                                                                                                                                                                                                               |
| HR+                                      | hormone receptor positive                                                                                                                                                                                                                                                                                                                                                                          |
| IB                                       | investigator's brochure                                                                                                                                                                                                                                                                                                                                                                            |
| ICF                                      | informed consent form                                                                                                                                                                                                                                                                                                                                                                              |
| ICH                                      | International Council for Harmonisation                                                                                                                                                                                                                                                                                                                                                            |
